### Study design

The study will not involve complications for participants, but if there is extreme difficulty with cooperation for participants the test will be discontinued. All participants were informed both orally and in writing about the study process. Written consent to participant were obtained before the study start. There is no criteria for intervention modification in this study protocol. To improve adherence to intervention protocols, every training session the examiner provide feedback to all participants and inform them about the training progress. The rehabilitation sessions and duration are flexible for participant.

We randomly assigned participants in 1:1 ratio, intervention and control group. The intervention group undergo the rehabilitation training program.

The two groups were matched for age and gender. Those in the control group do not receive any rehabilitation programs during the study. The randomization was applied by random number table (those assigned an odd number, control group; those assigned an even number, intervention group).

***Study procedures***. Pre-rehabilitation, the SNR (50%) of all participants was measured using the word in noise (WIN) test. In addition, a binaural TFS test and the SSQ questionnaire score of all participants are evaluated (see section
*Outcomes* below).

***Rehabilitation training***. Participants identify the set of 16 consonants using one-interval forced-choice procedure and feedback with correct answer. On each test the participants select one of the stimuli from the set of 16 syllables. The participants are informed while the stimulus is presented that they should identify its middle consonant. Following each stimulus presentation, a 4 × 4 visual display of the response alternatives appear on a computer monitor and the participant select the response by using the computer mouse.

Each participant select a box, if they click the box correctly, the box turn green and if they choose the wrong answer, the box turn red. The participant is given visual feedback by showing the correct VCV with a yellow box. No time limit is be imposed on the participant's responses. Each experimental run consists of 64 trials derived from a different random-order presentation of the 64 syllables in the stimulus set. Each run is last 16 to 30 min depending on the participant's response time. The total duration of rehabilitation sessions are e five weeks. Experiments are controlled by a desktop PC.

Only the intervention group undergo the rehabilitation and control group is not informed about details of the intervention study procedure.

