### Terminology used in this study

*Mild to moderate hearing loss:* auditory thresholds ≤25dB within the frequency<2000 Hz and 25–70 dB HL with frequency 2000–8000 Hz.

*TFS-LF test:* software designed by Hopkins and Moore in 2010. The test is originally based on measuring the interaural phase differences
^15^.

*Interaural phase difference (IPL):* lowest difference in the phase of the wave in each ear and dependent frequency sound waves and difference in time between ears
^15^.

*Signal to noise ratio (SNR):* ratio of the power of a signal (meaningful information) to the power of background noise (unwanted signal), expressed in decibels (dB). Larger numbers for signal characteristics mean better and more useful than unwanted noise information
^23^. In this study the signal-to-noise ratio levels were 0, 4, 8, 12, 16, 20, and 24 dB.

*Speech in noise score:* measured by Persian version of WIN test (PARWIN list), which is expressed as a percentage by performing a single syllable word test. The PARWIN test is a version of the Richard H. Wilson WIN test, in which the background noise in this test is baffled noise
^24^. PARWIN test is used to estimate SNR (50%) using Spearman Karber equation.

*Speech, Spatial and Qualities of Hearing Scale (SSQ) questionnaire:* used in previous studies in elderly individuals with communication disorders caused by hearing loss. From the original version of the SSQ questionnaire, its validity and reliability native version were confirmed (validity, 96% reliability) and included 47 items in three subgroups of speech perception, spatial hearing, and auditory quality. Based on the results of the questionnaire, the mean score of each item and item of each index will be measured for the research participants.

*Rehabilitation training:* auditory rehabilitation was based on TFS. The intervention group will be asked to identify vowel consonant vowel words (VCVs) that have only TFS preserved and their envelope discarded. It is based on that VCVs that processing and converting to TFS speech. In this process the ENV of VCVs are eliminated and only TFS will be kept.

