### Speech stimulus process

The TFS speech consists of single syllable recorded in / a / C / a / with various 16 consonant format which included Aja, Aka, Ara,…. and it is pronounced by a native-speaking man. The analogue signals are converted to digital a 16-bit at 44.1 KHz sampling frequency. The stimulus synthesis process is performed in MATLAB software and the software is provided in C programming language.

The original bandpass is filtered into 16 bands of equal bandwidth on a log frequency scale spanning 80 to 8020 Hz. Each Bandpass signal is decomposed to ENV and TFS by Hilbert transform. The ENV component is discarded and TFS component is normalized and TFS component in each band summed lastly creating TFS speech.

After rehabilitation, the SNR (50%) using the WIN test, and a binaural TFS test and SSQ questionnaire will be evaluated again in intervention group. Results will be compared in intervention and control groups before and after the rehabilitation program.

***Outcomes***.
*SNR (50%):* single syllable words in the presence of noise at different signal-to-noise ratios (0, + 4, + 8, + 12, + 16, + 20, + 24) as binaural in two study groups and compare the SNR (50%). Differences in scores before and after rehabilitation training between the two groups will be compared.

The Words-in-Noise (WIN) materials were developed to evaluate the ability of listeners to understand words in multitalker babble. The WIN involves in which the level of the noise is fixed and five words are presented at seven signal-to-noise ratios from 24 to 0 dB in 4 dB decrements. The 35 words are spoken by a native male speaker. The metric of interest is the signal-to-noise ratio (S/N) at which recognition performance is 50%, which is a value determined with the Spearman Karber equation see (
*Extended data:* S2).

Binaural TFS test: determines the binaural change of phase difference at different frequencies in intervention and control groups before and after rehabilitation training.

The correlation between the results of speech perception test scores in the presence of noise with the results of binaural TFS test in the two groups after rehabilitation program will be assessed.

*SSQ questionnaire score:* provided to each group before and after rehabilitation training. Scores between intervention and control groups will be compared (
*Extended data:* S3).

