## Discussion

Elderly populations are growing rapidly worldwide, and this higher number of older individuals is associated with an increase in prevalence and incidence of age-related disorders. Age-related hearing loss (presbycusis) is one the most common disorders with an increase in age. Hearing loss has significant negative impact in quality of life in elderly population. It causes limitation of communication and social activity
^1^.

Speech perception in noisy environments is very serious difficulty with presbycusis, The presbycusis is known as damage of hair cells in cochlea
^5^. The hair cells damage with presbycusis mostly associated with deteriorate of temporal fine structure (TFS) information
^7^.

TFS is important when background sounds are present
^9^. Loss of speech perception in noisy environments with presbycusis is mostly caused by damage of processing of TFS information. Our study is based on improvment of TFS deficit in cochlea.

The rehabilitation training is based on identify vowel consonant vowel words (VCV). 

The test is performed in several sessions. The total time of test is three times every week for total fives week for all subjects but the time in every session is different between participants.

To evaluate the efficiency of rehabilitation training we used temporal fine structure sensitivity test (TFS test), Speech in noise test (SNR 50%) and Speech, Spatial and Qualities of Hearing Scale (SSQ) 

They are performed in both intervention and control group but at the end of study we measure only the tests in intervention population.

Initially TFS1 was developed by Moore and Sek (2009) in order to discriminate a harmonic complex tone from the same tones with all components shifted upwards by the same amount in hertz leading to an inharmonic tone. The TFS-LF was described by Moore and Hopkins (2010) to measuring thresholds for detecting changes in interaural phase difference ( IPD). Although the TFS-LF is used generally but it has a limitation. The frequency of the tones is fixed, for example at 250, 500 or 750 Hz and some old

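### The self-rated SSQ is at risk of inflation by expectation: only the trained arm has sessions and progress messages, yet the SSQ counts as efficacy evidence beside the performance tests

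*Protocol article*

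**What the plan says.** All references are to the protocol article.

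- **Feedback.** Study design says that "every training session the examiner provide feedback to all participants and inform them about the training progress". The reason given is "To improve adherence to intervention protocols".
- **Control condition.** The same section says: "Those in the control group do not receive any rehabilitation programs during the study". Under Rehabilitation training it adds: "Only the intervention group undergo the rehabilitation and control group is not informed about details of the intervention study procedure".
- **Information to participants.** "All participants were informed both orally and in writing about the study process". No sham, active comparator or participant blinding is described.
- **The SSQ.** Under Terminology used in this study, the SSQ is a questionnaire that "included 47 items in three subgroups of speech perception, spatial hearing, and auditory quality". Under Outcomes it is "provided to each group before and after rehabilitation training. Scores between intervention and control groups will be compared".
- **Its role.** The Discussion lists it with the performance tests: "To evaluate the efficiency of rehabilitation training we used temporal fine structure sensitivity test (TFS test), Speech in noise test (SNR 50%) and Speech, Spatial" (the quote breaks off within the name of the SSQ). The Abstract groups the three in the same way. Statistical analysis applies a 0.05 level to every test.
- **A conflict.** The paragraph just before Outcomes says the post-training WIN, binaural TFS and SSQ assessments are repeated in the intervention group. The Discussion says that end-of-study testing covers that group only.

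**The concern.** The SSQ asks people how well they hear. Participants were enrolled because they complain of difficulty in noise. One arm attends repeated sessions and is told by an examiner how the training is going; the other has nothing equivalent. Both are then to rate their own hearing. Keeping controls unaware of the procedural details does not hide from trained participants that they were trained.

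An SSQ gain could therefore arise without any change in hearing and still be reported as a benefit of rehabilitation. Analysis cannot remove this, because arm and feedback are completely confounded. WIN SNR (50%) and TFS-LF are performance measures and less exposed, although effort may differ between arms.

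**Working it through.** **1. Who receives the messages.** The feedback sentence speaks of all participants but ties the feedback to training sessions. Only the intervention group has such sessions, and controls receive no programme. That controls get no progress message is thus an inference from sentences read together, but a firm one.

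**2. Exposure before the final SSQ.** The Abstract and Discussion give three sessions a week for five weeks: 3 × 5 = 15 sessions, against 0 in the control arm. Study design calls sessions and duration flexible, so 15 is nominal. The post-training SSQ follows all of them.

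**3. Evaluable numbers.** The plan states 15 per group, allowing for 20% dropout: 15 × (1 − 0.20) = 12 evaluable per arm. The 15 itself cannot be re-derived, because no means or standard deviations are given.

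**4. Illustration of the consequence.** Nothing in the documents measures expectation bias, so the shift *b* (in SD units of the SSQ) is an **assumption**. Take a true SSQ effect of zero, equal variances and a two-sided two-sample t-test at 0.05. The test statistic is then noncentral t with 2n − 2 degrees of freedom and noncentrality b√(n/2). The chance of a significant difference is the probability that its absolute value exceeds the 97.5% point of the central t distribution. For n = 12 and b = 0.5, the degrees of freedom are 22 and the noncentrality is 0.5 × √6 = 1.22, which gives 21.6%.

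| Assumed shift b (SD) | 12 per arm | 15 per arm |
|---|---|---|
| 0 | 5.0% | 5.0% |
| 0.2 | 7.6% | 8.3% |
| 0.3 | 10.8% | 12.5% |
| 0.5 | 21.6% | 26.2% |
| 0.8 | 46.6% | 56.2% |

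The table shows what a given shift would do to the error rate. It is not evidence that a shift of any particular size will occur. The rate rises with sample size, as it does for any bias that more data cannot average out.

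**5. Whether the contrast will exist.** Outcomes plans a between-group SSQ comparison before and after training; two other places restrict post-training testing to the intervention group. If the restriction held, the SSQ result would be a single-arm before–after change, at least as open to expectation. The table above applies only if both arms are tested.

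**The case against.** Four objections deserve weight.

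- **Direction and certainty.** A reader might infer that the SSQ difference will certainly be inflated. The text does not support that: it says participants are told of their progress, not that the news is good. An honest report of poor progress could lower self-ratings. A risk, most plausibly favouring training, is all that can be claimed.
- **Main cause.** The exposure comes chiefly from comparing an openly trained arm with an untreated one. Trained participants would know their status, and could judge their progress from the on-screen right/wrong display, even if the examiner said nothing. This stands. A reader might infer that dropping the progress messages would make the SSQ contrast unbiased; it would not. How much they add to the open design cannot be found from the documents.
- **Purpose.** The feedback has a stated adherence aim, in a small trial that allows for 20% dropout. Treating it as part of the training package is a defensible choice, so removing it has a cost that the documents do not quantify. This stands, and limits how firmly the change can be urged.
- **Matters left open.** The article fixes no test order at the end visit, and rules of interpretation are often left to an analysis plan. That is fair: neither is an error in the text. With about 12 evaluable per arm, a non-significant WIN result would not show absence of benefit either. But the article does place the SSQ among the measures of efficacy without qualification, and the feedback procedure is stated, not omitted.

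**Conclusion.** The point holds as a risk of bias. The trained arm alone has examiner contact and progress messages before completing a subjective measure that is used beside the performance tests to judge efficacy. The likely direction favours training and the size is unknown. Under the assumed shifts of 0.2 to 0.5 SD, the false-positive rate for the SSQ would be about 8–22% with 12 per arm, or 8–26% with 15 per arm.

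The conclusion rests on two readings: that feedback is confined to training sessions, and that no participant blinding exists beyond what the article describes. It does not extend to a claim that the SSQ result is already invalid, or that WIN and TFS-LF are affected to the same degree. It is a modest, cheap improvement, and its main value is to limit what an SSQ result on its own can be used to conclude.

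**What to change.** 1. **Order.** Have the SSQ completed first at the end visit in both arms, before any test performance is seen.
2. **Interpretation.** State that the SSQ is supportive only, and that an SSQ gain without a gain in WIN SNR (50%) will not be reported as evidence that hearing in noise improved. Word this as a limit on the claim, since a non-significant WIN result would not prove lack of benefit.
3. **Feedback.** Where adherence allows, keep examiner comments to attendance and hold performance summaries until the SSQ, WIN and TFS-LF are complete. The automatic on-screen feedback, which is part of the training task, stays.
4. **Reconciliation.** Bring the statements that end-of-study tests are done only in the intervention group into line with the planned between-group comparison.

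**Cost.** These changes affect the session script, the visit order and the protocol text, and add no staff or visits. The article says that no further modifications are planned, so a new version would be needed. Study status says that allocation is still to come, although Study design describes it in the past tense. If training has already begun, items 1, 2 and 4 can still be adopted. The downsides are some possible loss of motivation from delayed summaries and a more cautious SSQ conclusion.

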## Abstract

**Background:** Age-related hearing loss (presbycusis) is a form of hearing loss in over 60-years-olds and has a negative impact on quality of life. Presbycusis is multifactorial and is predominately characterised with a loss of speech perception in noise. In the cochlea, auditory filters decompose broadband sound into a series of narrowband output signals, which contains two kinds of temporal information: slow changes in overall amplitude envelope (ENV) and faster variations in temporal fine structure (TFS). TFS is important for recognition of target speech in noise. The main aim of the study is to evaluate the effect of TFS rehabilitation training in participants over the age of 60 years with mild to moderate hearing loss.

**Methods:** A randomised clinical trial  conducted on 30 participants with mild (loss of 20-39dB HL) to moderate (40-69dB HL) hearing loss, aged between 60 and 75 years old. Participants with conductive hearing loss, abnormal middle ear pathology and central nervous system disease were excluded. Participants were selected randomly  to an intervention and control group with a 1:1 ratio. Rehabilitation for the intervention Group are 30-minute sessions three times a week for a total five weeks of vowel consonant vowel words that are used to eliminate ENV and keep only TFS. Word in noise test, binaural TFS test, and Speech, Spatial and Qualities of Hearing Scale scores are performed at the beginning and end of study to evaluate the effect of rehabilitation training.

**Conclusion: ** Life expectancy in the elderly has improved, leading to an increased prevalence of age-related diseases including presbycusis. A literature review highlighted that TFS damage is permanent; however, in this study we will attempt to prove that TFS training may lead to speech in noise perception improvement.

**Trial registration: **Registry of Clinical Trials,
IRCT2019625044006N1 (7
^th^ August 2019).

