### Objectives

The main aim of the study is to evaluate the impact of special rehabilitation training based on TFS on improvement of speech in noise perception in an elderly population with mild to moderate hearing loss.

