### Study overview

We conduct a randomised clinical trial of rehabilitation training on speech in noise perception performance on an elderly population with mild to moderate hearing loss at the Audiology Clinic of School of Rehabilitation Sciences, Iran University of Medical Sciences (Tehran, Iran). It is hypothesized that the inability to use TFS speech cues is the main cause of speech perception problem in noise in elderly individuals, and it is possible by designing appropriate rehabilitation exercises to reduce the difficulty of speech perception in noise.

The Medical Ethics Committee at the Iran University of Medical Sciences approved the registered study protocol (IR.IUMS>REC.1398.003). The study was registered on the Iranian Registry of Clinical Trials (registration number,
IRCT2019625044006N1), a Primary Registry in the World Health Organization Clinical Trials Registry Network.

The protocol does not involve complications for participants in the study. All participants were informed both verbally and in writing about the study procedure. Written consent to participants were obtained from the participants before the study start (see
*Extended data:* S1).

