listener have difficulty to perform the test with chosen frequency. This limitation led to develop TFS-AF test. In TFS-AF test IPD is fixed for example is 180 degree with frequency adaptively varied to determine a threshold. In this study, we used TFS-LF test in all participants because TFS-LF test provides a good measure of sensitivity to binaural TFS. The aim of this study was to improve speech in noise perception with fast transition consonant vowel words (VCV) and identify interaural phase difference (IPD) which TFS-LF is more appropriate. TFS-LF were performed in three frequencies, 250, 500 and 750 Hz
^15^. 

Signal-To-Noise Ratio (SNR) 50% is used routinely by audiology clinics. Age related hearing loss have decline speech discrimination ability in similar SNR compare to normal hearing ability and require higher SNR
^23^.

Several test and questionnaire are performed to assess the ability to hear and process sounds and speech from different locations which called spatial hearing speech. In this study we use The Speech, Spatial and Qualities of Hearing Scale (SSQ).

The validity of TFS-LF, SNR 50% and SSQ questionnaire to recognise hearing loss have been confirmed previously
^15,
22,
23^.

We designed stimulus software which divided sound signal to envelope (ENV) and TFS. In this program ENV is removed and only TFS is preserved.

In conclusion in this study, we will attempt to prove by special rehabilitation training based on TFS damage age-related hearing loss can be improved.

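### With a no-training control, the trial can show that the whole programme beats no training, but not that its temporal fine structure (TFS) content is what helped

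*Protocol article*

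**What the plan says.** All references are to the protocol article.

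**The control arm.** Study design states "Those in the control group do not receive any rehabilitation programs during the study", and adds: "Only the intervention group undergo the rehabilitation and control group is not informed about details of the intervention study procedure". No sham task, alternative listening task or other matched activity is described for controls.

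**The intervention arm.** The Abstract gives the schedule as "30-minute sessions three times a week for a total five weeks of vowel consonant vowel words". Study design describes the task: "Participants identify the set of 16 consonants using one-interval forced-choice procedure and feedback with correct answer". It also says that "every training session the examiner provide feedback to all participants and inform them about the training progress". Although that sentence speaks of all participants, it concerns training sessions, and controls have none.

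**The claims.**
- Objectives is to "evaluate the impact of special rehabilitation training based on TFS on improvement of speech in noise perception".
- Study overview is more mechanistic: "It is hypothesized that the inability to use TFS speech cues is the main cause of speech perception problem in noise in elderly individuals". The same sentence goes on to say that suitable exercises can reduce the difficulty.
- The Discussion says the study rests on improving a TFS deficit in the cochlea, and closes with "we will attempt to prove by special rehabilitation training based on TFS damage age-related hearing loss can be improved".
- The Abstract conclusion also speaks of proof, though it says only that TFS training may lead to improvement.

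**The concern.** The arms differ in several things at once: TFS-only stimuli, repeated listening practice, trial-by-trial feedback and regular examiner attention. Randomisation makes the between-arm difference a fair estimate of the effect of all these together. It does not divide that effect among them.

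Parts of the article go further than the package. They name a cause (inability to use TFS cues) and a site of repair (the cochlea), and they undertake to prove that TFS-based training works. A positive result could then be reported as support for the TFS mechanism when the design leaves other explanations open. The outcomes make this a practical risk. SSQ is a questionnaire, and controls will know that they were not trained. SNR (50%) and the binaural TFS test are behavioural listening tests, on which practised or more attentive listeners might do better for reasons unrelated to TFS.

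**Working it through.** **1. Difference in exposure between the arms.** Inputs are from the Abstract and Study design.
- Sessions: 3 per week × 5 weeks = 15 in the intervention arm, 0 in the control arm.
- Training time at 30 minutes per session: 15 × 0.5 h = 7.5 h, against 0 h.
- Study design gives 16 to 30 minutes per run. If there is one run per session (an assumption, as runs per session are not stated), the lower limit is 15 × 16/60 = 4 h.
- Study design also calls sessions and duration flexible. The hours are therefore a range of roughly 4 to 7.5, while 15 is the scheduled number of sessions.

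**2. What the contrast identifies.**

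| Element | Intervention | Control |
|---|---|---|
| TFS-only speech | yes | no |
| Forced-choice consonant practice | yes | no |
| Correct-answer feedback on each trial | yes | no |
| Examiner feedback at each session | yes | no |
| Baseline WIN, binaural TFS and SSQ testing | yes | yes |

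The first four rows always change together. The difference between arms estimates their joint effect, and nothing in the design separates the first row from the next three.

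**3. What could follow if TFS content added nothing.** This is an illustration. The documents give no size for a non-specific benefit, so its standardised value *d* is assumed over a range.
- Sample size, from the Sample size section: 15 per group including 20% dropout, so 15 × (1 − 0.20) = 12 evaluable per arm. The 15 itself cannot be reproduced from the formula, because no means or standard deviations are printed. The point does not depend on it.
- Probability of a significant result favouring training (two-sided α = 0.05, normal approximation): Φ(d·√(n/2) − 1.96).
- Worked case, d = 0.5 and n = 12: 0.5 × √6 = 1.225, then 1.225 − 1.96 = −0.735, and Φ(−0.735) = 0.23.

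| Assumed non-specific benefit d | 12 per arm | 15 per arm |
|---|---|---|
| 0 | 0.025 | 0.025 |
| 0.3 | 0.11 | 0.13 |
| 0.5 | 0.23 | 0.28 |
| 0.8 | 0.50 | 0.59 |

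Using the t distribution at 12 per arm gives 0.10, 0.22 and 0.47 for the last three rows, so the message is the same. These would be true findings about the programme. They would be wrong only if read as findings about TFS.

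**4. The mechanism evidence that is planned.** Outcomes includes the binaural TFS test before and after training, and its correlation with speech-in-noise scores after the programme. A better TFS-LF result in the trained arm would be relevant, but practice or attention could improve both tests. A correlation after training is not a randomised contrast. A behavioural threshold for interaural phase also does not locate a change in the cochlea.

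**5. Whether the contrast exists at all.** The text just before Outcomes has the tests repeated in the intervention group, then says both groups are compared before and after. The Discussion says that at the end only the intervention group is measured. If controls are not retested, even the programme-level comparison cannot be made.

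**The case against.** The strongest reply is that a no-training control is a legitimate comparator and that much of the article asks only a programme-level question. Objectives concerns training based on TFS, which can fairly be read as the name of the programme. The second half of the hypothesis sentence is about exercises reducing difficulty, and the Abstract conclusion is hedged. This stands. The mismatch is confined to the causal half of the hypothesis, the Discussion's cochlear claim and the language of proof.

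Task familiarity is also a weaker rival explanation than it looks. Training is closed-set consonant choice, while the outcomes are words in babble, interaural phase detection and a questionnaire. None is the trained task. This also stands, but it leaves general listening practice, feedback and attention.

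A reader might infer more than the documents support:
- *That ordinary-speech training would give the same gain.* Nothing in the article shows this. It could not be excluded, and no more than that follows.
- *That controls have no contact.* They have no training contact, but they are tested at baseline.
- *That a control trained on the same syllables before envelope removal would isolate TFS.* Intact speech carries both envelope and TFS, so the contrast would test envelope removal. Such a task may also differ in difficulty. It would need extra sessions and would probably shrink the expected difference.

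**Conclusion.** The point holds as a limit on what may be concluded. It is not a fault in the choice of control. With 15 training sessions against none, a significant difference would support the statement that this programme improves the outcome relative to no training. It would not support TFS-only content as the active ingredient, inability to use TFS cues as the main cause, or improvement of a cochlear TFS deficit.

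The share of any gain that is due to TFS cannot be estimated from this design. The probabilities of 0.11 to 0.50 at 12 per arm rest on assumed non-specific benefits of 0.3 to 0.8. They show only that the alternative explanation is not negligible if such benefits exist. The verdict itself does not depend on them. Even the programme-level conclusion assumes that controls are retested, on which the article contradicts itself.

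**What to change.** Keep the two-arm design and change the wording.

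1. In the Abstract, Study overview and Discussion, state the tested hypothesis and planned conclusion as the effect of this training programme compared with no training. The TFS account can remain as the rationale.
2. Where the Abstract and Discussion set out to prove an effect, say that the study will evaluate it.
3. Add one sentence saying that the design cannot attribute a gain specifically to TFS, because the arms also differ in listening practice, feedback and examiner attention.
4. Describe the TFS-LF change and its correlation with SNR (50%) as exploratory, indirect evidence on mechanism.
5. Reconcile the text on post-training testing (the end of the Speech stimulus process text, Outcomes and the Discussion) so that it is clear whether controls are retested. The between-arm comparison requires it.

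Items 1 to 4 cost only wording, and the downside is a narrower conclusion. Item 5 is also only wording if retesting controls is already intended. If it is not, it adds one test visit for each control. A control trained on unprocessed syllables is not recommended, for the reasons given under the objection.
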